### Study Interventions

#### Control Intervention

Participants in the control group will only receive routine nursing care [34]. When patients are admitted to the hospital, apart from routine nursing related to patient treatment, nurses will provide a booklet to patients about gastric cancer and treatment introduction, adverse reactions of chemotherapy, nutrition management, exercise guidance, psychological support (eg, relaxation and music), and life guidance during chemotherapy. In addition, the researchers will contact patients by phone or WeChat every week and send relevant health education messages to reduce the dropout rate. The nurses will not provide patients with any training in communication skills and will not actively encourage couples to discuss cancer-related thoughts and feelings.

#### Experimental Intervention

The marital self-disclosure intervention is divided into 4 stages. Each stage will be divided into the chemotherapy and hospitalization phase and the interval and home phase. Both phases include verbal and written disclosures, and the intervention will be conducted in 16 weeks. The flowchart of the trial is shown in Figure 1.

**Figure 1 figure1:**
[figure not shown]
Flowchart of the trial. The primary outcome is the score of the Fear of Progression Questionnaire-Short Form (FoP-Q-SF) for patients. The secondary outcomes are the scores of the FoP-Q-SF for partners and the Dyadic Coping Inventory.

##### Phase 1: Development of the Marital Self-Disclosure Intervention

A previous systematic study [35] by our team found that the most common methods of couple communication are one-on-one and face-to-face communication. They should accept training in marital communication methods before marital self-disclosure, such as how to incorporate the materials from the course into their daily lives through the communication skills learned [36], the strategies for expressing their thoughts and feelings about cancer, and the strategies for accepting and affirming each other’s feelings and opinions [23]. Psychological evaluation indicators are stable, and no significant changes are observed in frequent evaluations [15]. Therefore, 3 to 5 weeks per session can obtain a trend change in the index and will not lead to patient evaluation fatigue, which involves better evaluation frequency. Patients with cancer become unwell due to chemotherapy, and short-term interventions (3-6 stages, 40-60 minutes each step) increase memory and application of what couples have learned and increase patient confidence and motivation to manage their disease [37]. In situations where disclosure to a partner becomes challenging or problematic, individuals may gain some benefit from writing a disclosure diary [15,38,39]. The researchers have developed and designed the intervention. The literature mentions the disclosure needs of cancer couples and the changes in cancer patients’ fear of recurrence during chemotherapy, and provides information on the interview framework, objectives, benefits, mechanisms, and strategies to implement marital self-disclosure. To further improve the marital self-disclosure intervention, the researchers will conduct in-depth interviews with 3 patients with gastric cancer and their spouses to explore the experiences and needs of marital communication. Furthermore, 6 nurses from the oncology ward will be interviewed to explore the intervention preference and obtain their suggestions for the content of marital self-disclosure. The findings of in-depth interviews will be used to improve the frame, stage, time, and disclosure process of marital self-disclosure.

##### Phase 2: Panel Evaluation by Experts

An expert panel will be invited to provide expert inputs for developing the marital self-disclosure intervention. The expert selection criteria are as follows: (1) medical staff specializing in oncology, the gastrointestinal system, and psychology; (2) educational background of a bachelor’s degree or above; (3) deputy senior title in a medical or nursing position or above; (4) rich experience in the above fields and ability to provide professional advice and guidance for this research; (5) working experience of more than 10 years; and (6) willingness to participate in this study. A total of 12 experts will be selected. Before the consultation, the research background and methods will be explained to the experts to obtain support and cooperation.

The contents and methods of marital self-disclosure are derived from the 2 phases mentioned above.

###### Chemotherapy and Hospitalization

The intervention time during hospitalization is the first day after chemotherapy, and the intervention is used once per chemotherapy for a total of 4 times for 45 to 70 minutes each time. The intervention includes verbal and written disclosures. The researcher will preside over the marital self-disclosure process and introduce it to patients with gastric cancer and their spouses (definitions of dyadic coping ability, marital self-disclosure, benefits, stages, process, techniques, and time). Both the patient and their spouse will take turns as speakers and listeners, and receive training or undergo review on marital self-disclosure skills for 5 to 10 minutes each time. The training or review details are shown in Table 1. The training will focus on emphasizing the strengths of dyadic coping and distinguishing between problem-solving and supportive communication. Couples will be encouraged to spend more time understanding each other through supportive communication rather than directly addressing communication issues. Couples will practice marital self-disclosure skills through 4 revealing themes. Couples will be encouraged to express their fear of cancer recurrence. When partners disclose information, supporters should allow the speakers to fully express their feelings and should respond positively to the messages of the speakers, showing empathy for them and acknowledging their points of view.

Each stage has different revealing goals, and the disclosure outline set according to the goals differs. The goals of the personal emotional expression stage are to reveal the person’s thoughts and feelings after the illness, reveal the person’s concerns about the progression of the disease, and express other emotions. The goals of the social cognition expression stage are to disclose the impact of cancer on family or social functioning after the illness, reveal the couple’s specific concerns about the progression of the disease, and express other emotions. The goals of the benefit discovery stage are to disclose the benefits of couples from the experience of illness, reveal positive emotions after the illness, and reveal positive changes that have occurred in their life during treatment. The outlook to the future stage aims to disclose the couple’s plans, reveal the couple’s needs, formulate a cancer recurrence prevention plan, and express other emotions. The patient with gastric cancer and their spouse will disclose information to each other according to the disclosure outline (20-30 minutes) at each stage. When one party is disclosing information, the other party is required to listen actively. After the verbal disclosure, the patient will participate in a written disclosure based on the given topics for 20 to 30 minutes each time. During the written disclosure, the researcher and the patient’s spouse are required to maintain silence and respond to the patient timely if there are any questions. After writing, the researcher will take back the notebook. The disclosure topics of the 4 stages are described in detail in Table 2.

**Table 1 table1:** Disclosure training of the speaker and listener.

Disclosure request	Description
Disclosure request of the speaker	Share a topic-related experience that evokes strong emotions Follow your heart and express your thoughts sincerely Tell your partner about the experience in as much detail as possible, including the event itself and psychological feelings Do not talk too much at one time; pause occasionally to give your partner a chance to show understanding and support
Disclosure request of the listener	Try to stand in your partner’s role and understand their experience Avoid immediately solving the problem or giving advice, focus the conversation on how your partner feels, reveal your thoughts when necessary, and facilitate the expression of your partner Listen reflectively, summarize what your partner has said, pay attention to your tone of voice, maintain eye contact, and nod your head to show understanding

**Table 2 table2:** Marital self-disclosure topics.

Theme and aspects		Description
**First chemotherapy: personal emotional expression**		
	Verbal disclosure goals (couple)	Reveal the person’s thoughts and feelings after the illness Reveal the person’s concerns about the progression of the disease Express other emotions
	Disclosure outline	How have you felt since (your partner) became ill? Are you worried about the progression of the disease? What are the specific aspects? What other emotions did you experience during the treatment?
	Written disclosure (patient)	Please write down your inner thoughts and feelings during the illness and how they affect you
**Second chemotherapy: social cognition expression**		
	Verbal disclosure goals (couple)	Disclose the impact of cancer on family or social functioning after the illness Reveal the couple’s specific concerns about the progression of the disease Express other emotions
	Disclosure outline	What impact does the illness (of your partner) have on your family, work, and social interactions? Are you worried about the progression of the disease? What are the specific aspects? What other emotions did you experience during the treatment?
	Written disclosure (patient)	Please write down the couple’s specific concerns during the illness and how they affect you
**Third chemotherapy: benefit discovery**		
	Verbal disclosure goals (couple)	Disclose the benefits for couples from the experience of the illness Reveal the positive emotions after the illness Reveal the positive changes that have occurred in your life during treatment
	Disclosure outline	Did you benefit from the experience of being sick? What are the specific aspects? What are the good influences on you? What positive emotions did you experience after (your partner) got sick? What positive changes have you made during the (partner) treatment?
	Written disclosure (patient)	Please write down the positive changes and emotions that you have experienced from the illness
**Fourth chemotherapy: outlook to the future**		
	Verbal disclosure goals (couple)	Disclose the future plans of the couple Reveal the needs of the couple and formulate a cancer recurrence prevention plan Express other emotions
	Disclosure outline	What are your plans for the future? What other needs do you have for preventing disease recurrence and what are your plans to prevent the recurrence of the disease? What other emotions did you experience during the treatment?
	Written disclosure (patient)	Please summarize and write about your cancer recurrence prevention plan and hopes for the future

###### Chemotherapy Interval and Homework

With regard to homework requirements, couples will determine the time of disclosure according to the actual situation. The verbal and written disclosures will be conducted at least once a week for 20 to 30 minutes each time. The disclosure outline during the chemotherapy interval is the same as that during the chemotherapy. At the end of every stage, a notebook will be provided to the patient, and the patient will be required to complete homework after chemotherapy.

##### Phase 3: Marital Self-Disclosure Intervention Workshop for Facilitators

First, 2 oncology nurses with strong nursing and communication skills will gain the trust of patients, screen patients who met the inclusion and exclusion criteria, ask them whether they are willing to participate in this study, and assist the consenting patients in signing the informed consent form. Second, participants in the experimental group will receive the marital self-disclosure intervention delivered by 2 communication-led nurses who have master’s degrees in nursing and who are certified psychological counselors. The communication-led nurse will (1) prevent negative interactions; (2) use the checklist to facilitate the disclosures of patients and their spouses; (3) ensure that the communication does not deviate from the outline; and (4) guide the disclosure content to focus on the speaker’s experience. Furthermore, the research nurse will (1) add the WeChat ID of the patient or spouse; (2) provide weekly WeChat reminders; and (3) require the patient or spouse to take photos, upload data, and check in regarding the disclosure execution status and disclosure diary through WeChat. If patients have any nursing or treatment questions, they can consult the research nurse through WeChat. For patients who do not have WeChat, the nurse will follow-up on the implementation status through telephone contact. Moreover, the nurse will record the reasons for patient dropout.

### Instruments and Measures

#### Sociodemographic and Clinical Variables

Variables include the demographic information of patients with gastric cancer and their spouses, including age, gender, education level, employment status, family per capita monthly income, duration of the marriage, and fertility status (couple). In addition, information on clinical variables, including pathological classification, tumor stage, treatment type, and time since cancer diagnosis (patient), will be collected.

#### Fear of Cancer Recurrence for Patients

The FoP-Q-SF is a 1-dimensional scale based on the Fear of Progression Questionnaire (FoP-Q). The FoP-Q-SF for patients includes 12 items, which are rated on a 5-point Likert scale (1 point indicating “never” and 5 points indicating “always”), with a total score ranging from 12 to 60 and with higher scores indicating higher fear of disease progression [40]. Wu et al [41] translated the scale into Chinese and tested its reliability and validity. The authors found that the Cronbach α coefficient of the total scale was 0.886 and the Guttman split-half coefficient was 0.855. Moreover, the Cronbach α coefficients of the 2 extracted common factors were 0.836 and 0.804, respectively, and the Guttman split-half coefficients were 0.806 and 0.828, respectively, which indicated good content consistency and met the requirements of psychometrics.

#### Fear of Cancer Recurrence for Partners

The FoP-Q-SF for partners was developed by Zimmermann et al [42] based on the structure of the FoP-Q-SF scale to assess the degree of partners’ fear of disease progression in patients. The FoP-Q-SF for partners includes 12 items, which are rated on a 5-point Likert scale (1 point indicating “never” and 5 points indicating “always”), with a total score ranging from 12 to 60 and with higher scores indicating higher fear of their spouses’ disease progression. The Cronbach α coefficient of the scale was 0.88. Wu et al [41] translated the scale into Chinese and tested its reliability and validity. The authors found that the Cronbach α coefficient of the total scale was 0.834 and the Guttman split-half coefficient was 0.818. The Cronbach α coefficients of the 2 extracted common factors were 0.835 and 0.699, respectively, and the Guttman split-half coefficients were 0.774 and 0.721, respectively, which indicated good content consistency and met the requirements of psychometrics.

#### Dyadic Coping Ability

The DCI based on the system interaction model was initially developed by Bodenmann [43], which included 6 dimensions (55 items) and used a 5-point Likert scale. After further improvement, the DCI [44] was revised to 37 items and was measured on a 5-point Likert scale ranging from 1 (not at all/very rarely) to 5 (very often). To assess the stress and coping behaviors of couples, the DCI includes 5 subscales for the patient and a corresponding subscale for the partner: (1) stress communication by self; (2) emotion-focused supportive dyadic coping by self; (3) problem-focused supportive dyadic coping by self; (4) delegated dyadic coping by self; and (5) negative dyadic coping by self. The DCI also assesses 2 common dyadic coping behaviors: emotion-focused common dyadic coping and problem-focused common dyadic coping. Xu et al [45] translated this questionnaire into Chinese. The Cronbach α coefficient was 0.73.

### Outcome Assessment

Permission to adopt the 3 questionnaires has been obtained from the original researchers. A trained researcher will assess the outcomes, including sociodemographic variables and psychosocial variables. The sociodemographic variables include demographic and clinical characteristics. The psychosocial variables include fear of cancer recurrence for patients, fear of cancer recurrence for partners, and dyadic coping ability. The psychosocial variables will be repeatedly collected at 3 time points: baseline, after the second session of the intervention (nearly 2 months after baseline), and after the last intervention (almost 4 months after baseline). The control group will be reassessed at the same intervals. Furthermore, participants in the experimental group will be assessed to determine their experiences with the intervention after the last intervention session (Table 3). The conceptual framework is shown in Figure 2.

**Table 3 table3:** Study measures.

Variable	Outcome (measure)	Time point		
		Baseline	2 months after baseline (after the second intervention)	4 months after baseline (after the fourth intervention)
Inclusion criteria	Sociodemographic and clinical information	Yes	No	No
Primary outcome	FoP-Q-SF^a^ for patients	Yes	Yes	Yes
Secondary outcome	FoP-Q-SF for partners and Dyadic Coping Inventory	Yes	Yes	Yes
Intervention experience	In-depth interview	No	No	Yes

^a^FoP-Q-SF: Fear of Progression Questionnaire-Short Form.

**Figure 2 figure2:**
[figure not shown]
Conceptual framework.

### Data Collection and Compensation

Upon agreeing to participate in the study, participants will be required to complete a paper-based baseline survey questionnaire. Participants in the intervention group will have the option to receive the marital self-disclosure intervention directly after completing the survey, while participants in the control group will only receive routine care. Both groups of participants will be tracked for a duration of 16 weeks after recruitment, and data will be collected at 3 time points: baseline and 2 and 4 months postintervention.

To ensure participant confidentiality, information collection will be restricted to face-to-face communication and a paper-based questionnaire. Birth dates or participant addresses will not be collected. All data will be stored on secure internal platforms of Hospitals A and B. At the end of the study period, only researchers will have access to the data set.

At each time point, the research team will contact participants via phone or WeChat, according to their preferences. Participants will be notified of upcoming follow-up studies and will be assisted in completing subsequent survey questionnaires. Upon completing each survey, they will receive small gifts, such as a hand sanitizer. Recruitment is expected to last for 12 months, with an additional 16 weeks needed for follow-up with all recruited participants to complete data collection. Data analysis will commence at the end of recruitment.

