**Methods:**

This is a quasiexperimental study with a nonequivalent (pretest-posttest) control group design. The study will be conducted at 2 tertiary hospitals in Taizhou City, Jiangsu Province, China. A total of 42 patients with gastric cancer undergoing chemotherapy and their spouses will be recruited from each hospital. Participants from Jingjiang People’s Hospital will be assigned to an experimental group, while participants from Taizhou People’s Hospital will be assigned to a control group. The participants in the experimental group will be involved in 4 phases of the marital self-disclosure (different topics, face-to-face) intervention. Patients will be evaluated at baseline after a diagnosis of gastric cancer and reassessed 2 to 4 months after baseline. The primary outcome is the score of the Fear of Progression Questionnaire-Short Form (FoP-Q-SF) for patients. The secondary outcomes are the scores of the FoP-Q-SF for partners and the Dyadic Coping Inventory.

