## Results

The research activities for this study commenced in October 2022. Participant recruitment and data collection began in February 2023, with the expectation of completion within 12 months (by December 2024). As of October 30, 2023, a total of 97 gastric cancer patients and their spouses have been recruited, and all baseline data have been collected. Once sufficient participants are recruited, subsequent measures will be performed and data analysis will commence. The primary results of this study are anticipated to be announced in June 2024.

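### Analysis is timed to the end of recruitment, 16 weeks before follow-up is complete, and the Results section ties follow-up visits to recruitment instead of to each participant's baseline

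*Protocol article*

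**What the plan says.** **Start of analysis.** Data Collection and Compensation gives the calendar: "Recruitment is expected to last for 12 months, with an additional 16 weeks needed for follow-up with all recruited participants to complete data collection". The next sentence reads: "Data analysis will commence at the end of recruitment".

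**Visit schedule.** Outcome Assessment and Table 3 place the patient and partner fear scores and the Dyadic Coping Inventory at baseline, after the second session (about 2 months after baseline) and after the last session (about 4 months after baseline), with the control group at the same intervals. Data Collection and Compensation agrees that follow-up runs per participant: "Both groups of participants will be tracked for a duration of 16 weeks after recruitment".

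**Status report.** The Results section uses a different trigger: "Once sufficient participants are recruited, subsequent measures will be performed and data analysis will commence". It gives the enrolment to date: "As of October 30, 2023, a total of 97 gastric cancer patients and their spouses have been recruited", with all baseline data collected.

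**Target.** The Abstract states: "A total of 42 patients with gastric cancer undergoing chemotherapy and their spouses will be recruited from each hospital". Methodology and Design and Sample Size give the same 42 per group.

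**Calendar.** The Results section starts recruitment and data collection in February 2023, expects them to finish in 12 months, glosses this as December 2024, and announces primary results for June 2024.

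**The concern.** The start of analysis and the timing of the primary measurement are basic rules of a trial, and here each is stated in two ways that do not agree.

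If the analysis began when recruitment closed, the most recently enrolled couples could not yet have a 4-month score. The Data Analysis section plans a two-way repeated-measures ANOVA over baseline, 2 and 4 months on an intention-to-treat basis. In its conventional form that method needs all three scores, so late recruits would drop out of the comparison because of the calendar alone.

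If follow-up measures waited until recruitment was judged complete, early couples would be measured well beyond 2 and 4 months and late couples on time. Time since baseline would then vary widely within a single labelled time point.

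The word *sufficient* adds to the uncertainty. The plan names a number, the count already exceeds its total, and the text still treats recruitment as unfinished without saying what it is waiting for.

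**Working it through.** **1. The plan's own target.** Sample Size gives 35 per group plus 20% for dropout: 35 × 1.20 = 42 per group, and 2 × 42 = 84 couples. The stated figure is reproduced.

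**2. Share without the 4-month score if analysis starts when recruitment ends.** Inputs: 12 months of recruitment (52 weeks) and 16 weeks of follow-up per participant, both from Data Collection and Compensation. Assumption: even accrual. Participants enrolled in the last 16 weeks are incomplete.
- Share: 16/52 = 0.31.
- Of 84: 84 × 16/52 ≈ 26 incomplete, 58 complete, or about 29 per group if evenly split. This is below the 35 in Sample Size, before any dropout.
- Of 97: 97 × 16/52 ≈ 30 incomplete, 67 complete, or about 34 per group if evenly split.

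The share depends on the length of recruitment: a longer period makes it smaller, a shorter one larger. If recruitment had closed on 30 October 2023, 244 to 271 days after a start in February 2023 (the day is not given), the share would be 112/271 = 41% to 112/244 = 46%.

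The 16 weeks follow Outcome Assessment and the per-participant tracking period. Three other places (Methodology and Design, Data Collection and Compensation, Data Analysis) count the 2 and 4 months from after the intervention. Since the intervention itself takes 16 weeks, that reading would lengthen the gap to about 32 weeks.

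**3. Visit timing under the Results wording.** A couple enrolled in February 2023 was due its 2-month measure in April 2023 and its 4-month measure in June 2023. On 30 October 2023, anyone enrolled before 10 July 2023 (16 weeks earlier) was past 16 weeks. With even accrual:
- start on 1 February: (271 − 112)/271 × 97 = 57 of 97;
- start on 28 February: (244 − 112)/244 × 97 = 52 of 97.

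So roughly 52 to 57 couples were already due their last measure on a date when the text still places the follow-up measures in the future. A rule that waits for recruitment and a rule that follows each baseline cannot both be applied.

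**4. Enrolment against target.** 97 − 84 = 13, and 13/84 = 15.5% over the total. The target is per hospital, however. Since 97 − 42 = 55, a site with more than 55 would leave the other below 42. The total alone does not show that both groups are full.

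**5. Calendar.** February 2023 + 12 months = February 2024. Adding 16 weeks gives 23 May to 19 June 2024. December 2024 is 22 to 23 months after the start and falls after the June 2024 announcement. The Abstract has enrolment and data collection both finished in 12 months, whereas Data Collection and Compensation needs 12 months plus 16 weeks.

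**The case against.** The strongest reply is that this is loose drafting. The authors plainly know about the extra 16 weeks, because they state them in the sentence just before the one at issue. The planned ANOVA needs the 4-month score, so the effect analysis could hardly be run properly without it. Baseline description and baseline group comparisons, also in Data Analysis, can legitimately begin when recruitment ends. Completion of follow-up between late May and mid-June 2024 also fits a June 2024 announcement. All of this is fair, and it makes analysis after full follow-up the more likely intention. It does not remove the contradiction: the sentence is not limited to baseline analyses, and the Results section repeats the same trigger.

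On visit timing, the reply is that the Methods text, Table 3 and the link to chemotherapy sessions all anchor the measures to the individual, against one status sentence in Results. That also stands, and it limits the point to a conflict of wording.

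A reader might infer three stronger things: that an early look at outcomes was planned, that follow-up was in fact deferred, and that recruitment was continuing in the light of results. The documents support none of them. No interim comparison is described. The Results sentence does not show that any visit was late. The 97 is not split by hospital, so *sufficient* may simply mean filling a site still below 42.

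**Conclusion.** The concern holds as a contradiction in stated rules. The start of analysis conflicts with the follow-up period stated one sentence earlier. The Results wording on follow-up measures conflicts with Outcome Assessment and Table 3. The enrolment of 97 against 84 is left without a split by hospital, a revised target or an explanation.

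Followed literally, the first conflict would leave about 31% of participants without the 4-month primary score, more than the 20% allowed for dropout. That figure rests on even accrual over 12 months and on 16 weeks of follow-up from baseline. The 52 to 57 couples past 16 weeks rest on even accrual from some day in February 2023. Both figures measure what the literal wording would do, not what was done.

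The December 2024 date is a minor reporting slip with no bearing on inference. The point should be corrected because the rules are wrong as written and rewording them costs almost nothing.

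**What to change.** - **Data Collection and Compensation:** state that between-group analysis of outcomes starts only after the last enrolled participant's 4-month assessment. Baseline description may start earlier if the text says so.
- **Results:** state that the 2- and 4-month measures follow each participant's own baseline date, in line with Outcome Assessment and Table 3.
- **Results:** replace *sufficient* with the stated target of 42 per hospital, or explain the excess over 84 by site.
- **Results:** reconcile December 2024 with 12 months from February 2023 and with the June 2024 announcement.

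The cost is wording, plus a start of outcome analysis up to 16 weeks later than the literal text. With recruitment closing in February 2024, the last assessment falls between 23 May and 19 June 2024, so a June 2024 announcement would be tight and may need to move.
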